### Calculation of dialysis dose

The dialysis dose will be calculated differently according to the type of modality. In the case of CVVH, solute transport is achieved by pure convection. The solute flux across the membrane is proportional to the ultrafiltration rate (Qf) and the ratio between the concentration of the solute in the ultrafiltrate and in plasma water (sieving coefficient S). For solutes freely crossing the membrane, S values are equal or close to 1. Because clearance is calculated from the product Qf × S, when S is proximal to 1, as for urea, clearance is assumed to be equal to Qf, provided that replacement solution is given in postdilution mode. For diffusive techniques (IHD or CVVHD), the clearances will be calculated on the basis of the delivered operational parameters on an experimentally constructed relationship (blood flow versus clearance) at three different dialysate flow rates (in CVVHD at 1 and 2 l/hour) for each given haemodialyzer. In mixed convective/diffusive techniques (e.g. CVVHDF), this relationship will constructed at two dialysate flows (1 and 2 L/hour) and at three ultrafiltration rates.

### Statistical analysis

#### Primary end-point

The power for a test of the null hypothesis (logistic regression, one continuous predictor) was calculated as follows. The one goal of the proposed study was to test the null hypothesis (i.e. that there is no relationship between clearance and event rate). Under the null condition, the event rate (0.51) is the same at all values of clearance or, equivalently, the odds ratio is 1.0, the log odds ratio (beta) is 0.0 and the relative risk is 1.0.

Power is computed to reject the null hypothesis under the following alternate hypothesis. For clearance values of 29.8 and 35.0, the expected event rates are 0.51 and 0.25. This corresponds to an odds ratio of 0.32, beta (log odds ratio) of -0.22, and a relative risk of 0.49. This effect was selected as the smallest effect that would be important to detect, in the sense that any smaller effect would not be of clinical or substantive significance. It is also assumed that this effect size is reasonable, in the sense that an effect of this magnitude could be anticipated in this field of research. In these computations, we assume that the mean clearance value will be 29.8 with a standard deviation of 10.0, and that the event rate at this mean will be 0.51 (Figure 3).

The sample size will be of a total of 110 patients.

Alpha and tails. The criterion for significance (alpha) has been set at 0.01. The test is two-tailed, which means that an effect in either direction will be interpreted (Figure 4).

Power. For this distribution (clearance mean of 29.8, standard deviation of 10.0), baseline (mean event rate of 0.51), effect size (log odds ratio of -0.22), sample size (*n *= 110) and alpha (0.01, two-tailed), the power is 1.00. This means that close to 100% of studies would be expected to yield a significant effect, rejecting the null hypothesis that the odds ratio is 1.0 [13-16]. The software used will be Epi Info (Utilities StatCalc Epi Info™ version 3.3, release date: 5 October 2004; Division of Public Health Surveillance and Informatics, Centers for Disease Control and Prevention, Atlanta, GA, USA) [17] and Power And Precision™ (version 2.0; release date: 20 December 2000) [18].

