• Delivered duration (hours; only at assessment time 24 or last assessment time before treatment interruption/end),

• Prescribed blood flow rate (ml/min; only at assessment time 0),

• Prescribed effluent (ml/hour; only at assessment time 0),

• Delivered effluent (ml/ 24 hour; only at assessment time 24 or last assessment time before treatment interruption/end),

• Prescribed reposition rate (ml/hour),

• Delivered reposition rate (ml/24 hours; (only at assessment time 24 or last assessment time before treatment interruption/end),

• Dialysate (ml/24 hours; only at assessment time 24 or last assessment time before treatment interruption/end),

• Total volume removed from the patient (ml/24 hours; only at assessment time 24 or last assessment time before treatment interruption/end),

• Type of haemodialyzer (as above),

• Surface (m^2^),

• Type of buffer,

• Anticoagulation (as above),

• Arterial site of vascular access (as above),

• Venous site of vascular access (as above),

• Type of vascular access (as above),

• Vascular access gauge,

• Treatment interrupted (date/time),

• Resumption of treatment (specify date/time),

• End (day/time),

• Change of modality.

Independently of modality chosen, all 'Modality-specific assessment time' CRFs include the following additional fields:

• SOFA (full set of data; only at assemement time 24 and for multiples of 24),

• Creatinine,

• Urea,

• Na,

• K,

• White blood cells (10^3^/μl),

• Platelets (10^3^/μl),

• Hb,

• pH,

• PaO_2_,

• PCO_2_,

• Bicarbonate,

• FiO_2_,

• Body temperature,

• Urine volume,

• Fluid balance (only at assessment time 24),

• Bicarbonate,

• Fractional inspired oxygen,

• Urine volume (ml/24 hours),

• Fluid balance (ml/24 hours),

• Systolic blood pressure (mmHg),

• Diastolic pressure (mmHg),

• Mixed venous oxygen saturation,

• Heart rate,

• Cardiac output,

• Cardiac index

• Pulmonary artery pressure,

• Systemic vascular resistance index,

• Intravascular blood volume index,

• Extravascular lung water index,

• Stroke volume variation,

• Vasopressor administration (milligrams of vasopressors/previous 24 hours): adrenaline (μg/kg per min), noradrenaline (μg/kg per min), dobutamine (μg/kg per min), dopamine (μg/kg per min), vasopressin (units/previous 24 hours), terlipressin (mg/previous 24 hours),

• Vasodilator administration,

• Other treatments: steroids (mg/24 hours; specify what type), recombinant human activated protein C, antithrombin III, protein C,

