### Study limitations

This will be an observational study. Based on the conventional meaning [19], an observational study cannot modify actual practice or therapy. In this study, the decision as to whether RRT should be commenced is at the discretion of the attending physician.

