## Discussion

The practice of CRRT has been subject to much debate. Only a few prospective randomized studies have been performed and published on the relationship between CRRT and outcome, and so conclusions are difficult to draw [20,21]. As emphasized in a recent editorial [22], in the field of artificial organs, prospective observational studies, despite their inherent limitations, have been performed because they are more affordable but are also capable of providing useful information from practical and medical standpoints.

Guerin and coworkers [23] studied 587 patients requiring haemodialysis and followed them until hospital discharge. Among the 587 patients, 354 received CRRT and 233 intermittent RRT as first choice. CRRT patients had a greater number of organ dysfunctions on admission and at the time of ARF, as well as higher SAPS II. Mortality was 79% in the CRRT group and 59% in the intermittent RRT group. Logistic regression analysis showed decreased patient survival to be associated with SAPS II on admission, oliguria, admission from hospital or emergency room, number of days between admission and ARF, cardiac dysfunction at time of ARF, and ischaemic ARF. No underlying disease or nonfatal disease, and absence of hepatic dysfunction were associated with an increase in patient survival. The type of RRT was not significantly associated with outcome. Those authors concluded that RRT mode was not of prognostic value.

The largest observational study ever performed (the BEST Kidney) was recently completed and reported in part [24]. A total of 1743 consecutive patients, who either were treated with RRT (CRRT or IHD) or fulfilled predefined criteria for ARF, were studied. Importantly, the findings indicated a marked difference in mortality rates across the different ICUs, suggesting that the practice of RRT may yet exert an influence on mortality [[name], unpublished observation]. Increasing the dose to 35 ml/kg per hour would be associated with a significantly greater survival in all ARF patients. However, higher dialysis doses (45 ml/kg per hour) had no statistically significant impact in the ARF patients studied. However, in a subgroup analysis including only those patients with sepsis, there was a trend suggesting that this might be the case.

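### The only primary test stated regresses mortality on clearance alone, so in this non-randomised study it cannot show how delivered dose affects outcome

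*Protocol article*

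**What the plan says.** The section Statistical analysis, Primary end-point, opens with "The power for a test of the null hypothesis (logistic regression, one continuous predictor) was calculated as follows". It then ties that test to the purpose of the study: "The one goal of the proposed study was to test the null hypothesis (i.e. that there is no relationship between clearance and event rate". Significance is fixed next: "The criterion for significance (alpha) has been set at 0.01", and "The test is two-tailed, which means that an effect in either direction will be interpreted". No adjusted, stratified, propensity-based or centre-aware analysis appears anywhere in the article.

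The rest of the article bears on whether one predictor is enough:

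- Discussion, on a cited observational study of 587 patients: "CRRT patients had a greater number of organ dysfunctions on admission and at the time of ARF, as well as higher SAPS II". The same study found SAPS II on admission associated with worse survival.
- Discussion, on a second and larger observational study: "the findings indicated a marked difference in mortality rates across the different ICUs".
- Introduction: variability in extracorporeal treatment is attributed in part to local practice and centre experience.
- Conclusion: the ultimate goal is how the dose actually delivered may affect outcome.
- Materials and methods and the Admission form: centre code, SAPS II, SOFA and weight are all collected.

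**The concern.** In an observational study, the dose a patient receives reflects the patient's condition, the modality chosen and the habits of the unit. If any of these also predicts death, the slope of mortality on clearance mixes their effect with that of dose. It then shows whether patients who received more clearance fared differently. It does not show whether clearance made the difference.

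Two consequences follow. A significant primary result could not be read as an effect of dose, which is what the Conclusion asks for. The 1% error rate would also not hold for that question: confounding shifts the estimate, and treating patients of one ICU as independent understates its standard error when dose and mortality both vary by unit.

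**Working it through.** **1. The plan's own figures reproduce.** Inputs from the Primary end-point section: event rates 0.51 at clearance 29.8 and 0.25 at 35.0, SD 10.0, n = 110, two-sided alpha 0.01.

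- Odds ratio = (0.25/0.75)/(0.51/0.49) = 0.320.
- Beta = ln(0.320)/(35.0 − 29.8) = −0.219 per unit, or −2.19 per SD.
- Relative risk = 0.25/0.51 = 0.490.
- Power = Φ(√(n·p(1−p))·|beta·SD| − z) = Φ(√(110 × 0.51 × 0.49) × 2.19 − 2.576) = Φ(8.9) = 1.00. Simulated Wald tests (4,000 runs) also give 1.00.

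The power statement is arithmetically correct and is not in dispute.

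**2. An example in the article's Discussion.** In the 587-patient study, crude mortality was 79% on continuous RRT (n = 354) and 59% on intermittent RRT (n = 233).

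- Crude odds ratio = (0.79/0.21)/(0.59/0.41) = 2.6.
- Pooled rate = (0.79 × 354 + 0.59 × 233)/587 = 0.711.
- z = 0.20/√(0.711 × 0.289 × (1/354 + 1/233)) = 5.2.

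The article reports that in that study's logistic regression the type of RRT was not significantly associated with outcome. A one-predictor test would have rejected decisively where the multivariable one did not. With the same split and rates, z scales with √n: 5.23 × √(162/587) = 2.75 (p = 0.006, below 0.01) at n = 162, and 5.23 × √(110/587) = 2.26 (p = 0.024, above 0.01) at n = 110. The example concerns modality, not dose. It matters for dose because the section Calculation of dialysis dose derives clearance differently for each modality.

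**3. False-positive rate from severity.** The article gives no dose-severity correlation, so the values here are assumptions. Simulation: no true dose effect, event rate 0.51 at mean severity, 3,000 studies per cell, Wald test at two-sided 0.01.

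| Severity OR per SD | Correlation | Unadjusted, n = 110 | Unadjusted, n = 162 | Adjusted, n = 110 |
|---|---|---|---|---|
| 1.5 | 0.2 | 1.2% | 1.9% | 0.7% |
| 1.5 | 0.3 | 1.9% | 2.3% | 0.7% |
| 2 | 0.2 | 2.1% | 3.1% | 0.5% |
| 2 | 0.3 | 4.5% | 7.4% | 1.0% |
| 3 | 0.2 | 3.7% | 6.5% | 1.0% |
| 3 | 0.3 | 9.5% | 16.6% | 0.6% |

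At zero correlation the unadjusted rate stays near 1%. Because the test is two-sided, reversing the sign of the correlation gives the same rejection rates with the bias reversed. The adjusted column assumes that severity is fully measured.

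**4. Centre alone.** Assumptions: 10 to 20 centres, n = 110 to 160, dose ICC 0.2 to 0.5, mortality ICC 0.02 to 0.10, and centre effects on dose and mortality independent of each other. With centre ignored, the rejection rate is 0.9% to 2.7%.

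**5. What adjustment costs.** Let R² be the share of dose variance explained by the covariates. Power at n = 110 is Φ(√(110(1−R²) × 0.51 × 0.49) × 2.2 − 2.576). At R² = 0.5 this is Φ(5.6), still 1.00. For a much smaller effect (assumed odds ratio 0.5 per SD), power is 0.86 unadjusted and 0.75 at R² = 0.2.

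**6. Room for covariates.** Expected deaths: 0.51 × 110 = 56, 0.51 × 135 = 69, 0.51 × 162 = 83. At about ten deaths per term, that allows roughly 5 to 8 terms.

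**The case against.** The strongest reply is that the quoted sentence introduces a power calculation. Power is often computed for a simple model and the analysis then adjusted. A full analysis plan, not shown, may do so, and collecting SAPS II, SOFA, weight and centre code leaves that open. This stands in part: a reader might infer that the sponsor has decided against adjustment, and the article does not say so. But this is not simply a detail left out. The article states a model with its number of predictors, ties it to the study's one goal, and names no other primary test. The text on study limitations does not mention confounding.

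Other tempting inferences also go beyond the text:

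- *That sicker patients receive a different dose, or that the bias makes high dose look protective.* The Discussion compares modalities. No dose-severity correlation is given, and its sign is unknown.
- *That the physician-discretion sentence shows dose is chosen by severity.* It reads "the decision as to whether RRT should be commenced is at the discretion of the attending physician", which concerns starting RRT and not how much is given.
- *That dose is generally a unit habit.* The fixed 2 l/hour prescription is reported for Australian units, and the Introduction says that European information is scarce.
- *That severity at RRT start goes unrecorded.* The modality forms do restrict "SOFA (full set of data; only at assemement time 24 and for multiples of 24". The same forms, which open at time 0, also ask for blood gases, inspired oxygen, platelets, creatinine, urine volume, blood pressure and vasopressors without that restriction on most items.
- *That clustering alone invalidates the test.* That needs high ICCs for which the article gives no source.

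**Conclusion.** The point holds. The one primary test the article states would, if followed as written, give an association open to confounding by severity and centre, and so cannot answer the question set in the Conclusion. That rests on the article's own background and needs no assumption.

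The size does need assumptions. With a dose-severity correlation of 0.2 to 0.3 and a severity odds ratio of 2 to 3 per SD, false positives are about 2% to 10% at the stated primary sample of 110. They are about 3% to 17% at 162, which is the recruitment figure before dropout. The direction is undetermined. Severity is the larger problem in these scenarios; ignoring centre alone adds modest inflation, to about 1% to 3% under moderate ICCs. Adjustment brings the rate back to about 1% only as far as the recorded scores capture severity, so residual confounding would remain a limitation.

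**What to change.** State the primary model as a logistic regression of mortality on delivered dose, adjusted for a short prespecified set already collected: SAPS II, admission SOFA and body weight. Age needs no separate term, because it is a component of SAPS II (a property of the score that the article does not spell out). Account for centre with a random intercept or cluster-robust standard errors. Keep the number of terms to what the deaths in the analysed sample support: about 5 at n = 110, up to about 8 at n = 162. Report the one-predictor model as descriptive only, and name confounding under Study limitations.

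Severity at RRT start can be drawn from physiological items already on the time-0 form; a full extra SOFA there is optional.

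The cost is a paragraph of text and a small loss of precision. Power at the planned effect stays 1.00, so sample size is no reason to leave the covariates out. The loss would matter only if the true effect were far smaller than planned.

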#### Secondary end-point

Based on data from one participating center (Milan Niguarda), approximately 20% of all RRT-treated patients have high noradrenaline requirements. A sample size of 27 patients will have 80% power to detect a difference in means of 0.295 (e.g. a mean of 2.5 μg/kg per min, assuming a standard deviation for differences of 0.600, using a paired t-test with a 0.05 one-sided significance level). Therefore, a minimun of 135 patients should be enrolled. Assuming a 20% dropout rate, the minimum number of patients to be recruited is 162.

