**Methods:**

DO-RE-MI is an observational, multicentre study conducted in ICUs. The primary end-point will be the delivered dose of dialysis, which will be compared with ICU mortality, 28-day mortality, hospital mortality, ICU length of stay and number of days of mechanical ventilation. The secondary end-point will be the haemodynamic response to renal replacement therapy, expressed as percentage reduction in noradrenaline (norepinephrine) requirement. Based on the the sample analysis calculation, at least 162 patients must be recruited. Anonymized patient data will be entered online in electronic case report forms and uploaded to an internet website. Each participating centre will have 2 months to become acquainted with the electronic case report forms. After this period official recruitment will begin. Patient data belong to the respective centre, which may use the database for its own needs. However, all centres have agreed to participate in a joint effort to achieve the sample size needed for statistical analysis.

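### The recruitment target of 162 does not cover the stated 20% dropout: 135 was multiplied by 1.2 instead of divided by 0.8, which gives 169

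*Protocol article*

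**What the plan says.** The section on the secondary end-point, under Statistical analysis in the protocol article, builds the target in three steps.

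1. Evaluable patients: "A sample size of 27 patients will have 80% power to detect a difference in means of 0.295". The assumptions are a paired t-test at a one-sided 5% level and a standard deviation of the differences of 0.600.
2. Scaling to all patients: data from one participating centre put the share with high noradrenaline requirements at about 20%. The article concludes: "Therefore, a minimun of 135 patients should be enrolled".
3. Dropout: "Assuming a 20% dropout rate, the minimum number of patients to be recruited is 162".

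The Methods part of the abstract repeats the result as the requirement for the study as a whole: "at least 162 patients must be recruited". The primary end-point section states a sample size of 110, so the secondary end-point sets the target.

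**The concern.** Steps 2 and 3 do not agree. If 135 patients are the minimum needed and 20% of those recruited are lost, the number recruited must satisfy N × 0.80 ≥ 135. The figure 162 does not satisfy this. It adds 20% of 135 to 135, whereas a dropout rate removes 20% of the larger number recruited.

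Two things are at stake. The first is the study's most prominent planning figure, which does not follow from its own inputs. The second is the 80% power for the noradrenaline end-point, which a study recruiting exactly the stated minimum would not have under the stated assumptions.

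**Working it through.** **Inputs, all from the secondary end-point section:** mean difference 0.295; standard deviation of differences 0.600; paired t-test, one-sided alpha 0.05; 27 evaluable patients; share with high noradrenaline requirements 20%; dropout 20%.

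**Step 1: the 27 patients.** The standardised difference is 0.295/0.600 = 0.492. Power is P(T > t(0.95; n−1)), where T has a noncentral t distribution with n−1 degrees of freedom and noncentrality 0.492 × √n.

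| n | Power |
|---|---|
| 25 | 77.1% |
| 26 | 78.6% |
| 27 | 80.0% |

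The article's 27 is reproduced and is the smallest n that reaches 80%. There is no slack at this step.

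**Step 2: the 135 patients.** 27/0.20 = 135. Reproduced exactly.

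**Step 3: the 162 patients.**

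- 135 × (1 + 0.20) = 162. This reproduces the article's figure exactly.
- 135/(1 − 0.20) = 168.75, rounded up to 169. This is the number from which 135 remain after 20% dropout.
- Difference: 169 − 162 = 7 patients, or 7/162 = 4.3%.

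**What 162 delivers under the article's own assumptions.**

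- Remaining after dropout: 162 × 0.80 = 129.6, against 135.
- With high noradrenaline requirements: 129.6 × 0.20 = 25.9, against 27.
- Power at 26 patients: 78.6%, against 80.0% at 27, a loss of 1.4 points.
- Dropout that 162 does cover: 1 − 135/162 = 16.7%, against 20%.

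**Random subgroup size.** The number of patients with high noradrenaline requirements is not fixed. Treating it as binomial with probability 0.20:

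| Patients remaining | Chance of at least 27 in the subgroup | Average power |
|---|---|---|
| 130 (from 162 recruited) | 0.448 | 0.777 |
| 135 (from 169 recruited) | 0.534 | 0.791 |

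The two rows must be read together. Most of the risk of falling short of 27 comes from the random subgroup size and would remain with 169. The part due to the dropout formula is 0.791 − 0.777 = 0.014, again about 1.4 points.

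**The case against.** The arithmetic is hard to dispute; the case on the other side concerns its weight.

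- **The power statement is correct as written.** The article attaches 80% to 27 patients, not to 162 recruited. This is true. What fails is the step from 135 to 162, although the purpose of that step is to secure the 27.
- **The error is smaller than the uncertainty of the inputs.** The 20% share is approximate and comes from one centre. With 129.6 patients remaining, a share of 27/129.6 = 20.8% would already give 27. With a share of 19%, even 135 patients give only 25.7 (135 × 0.19), with power of about 78%. A standard deviation of 0.61 instead of 0.600 lowers power at n = 27 to 78.9%. All this stands and limits the practical importance. It does not make the stated figure follow from the stated inputs.
- **162 is a floor.** Both places word it as a minimum, so recruiting more is allowed and could absorb the gap. But a minimum should meet the assumptions it is derived from, and this one does not.
- **The primary end-point is unaffected.** Correct: 129.6 remaining exceeds the stated 110.
- **The 20% might mean an allowance added on top of 135.** The text calls it a dropout rate, which applies to those recruited. If an allowance was meant, the wording needs correcting instead.

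The article's brevity is no defence, since it prints both the inputs and the result.

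**Conclusion.** The concern holds. The figure of 162 is wrong as a target for 20% dropout; the inputs give 169. A study that recruits exactly 162 and loses 20% would have about 26 evaluable patients and 78.6% power for the noradrenaline end-point, not 27 and 80%. The effect is small, at 7 patients (4.3%) and about 1.4 points of power, and is confined to the secondary end-point and the overall recruitment figure.

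The conclusion takes the article's own 20% share, 20% dropout, mean difference and standard deviation at face value, and reads the dropout rate as a proportion of those recruited.

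**What to change.** Replace 162 by 169 (135/0.80) in the secondary end-point section and in the Methods part of the abstract. The cost is two figures in the text and 7 more patients.

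If the target is to stay at 162, there are two alternatives that need no extra patients:

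- state that 162 allows for 16.7% dropout; or
- keep the 20% dropout and state the power for the noradrenaline end-point as between 78% and 79%.
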